### Power of the trial and sample size

To calculate the sample size we used the primary outcome Constant Shoulder Score with a range from zero to 100 points. Using the mean values from the injured shoulder in a similar population after proximal humeral fractures, SD equals18 according to clinical experience [16, 43]. There are two groups to be compared: Intervention group and control group. The minimal clinically important difference has been decided to equal 10 points. Level of significance (α) equals 0.05. Given a power of 0.80 (β) the number required in each group is 51 patients. Due to a predicted loss of included patients during follow-up, we aim to include 60 patients in each group.

### Statistics

Statistical analyses will be performed with the SPSS 17.0 software or later version (SPSS Inc. Chicago, Illinois, USA). All outcomes will be reported as mean values and 95% confidence interval (95% CI) for both treatment groups and for each hospital separate, as well as for all hospitals together. In case of small data groups, bootstrapped 95% CI will be calcluated. Mean differences between the groups will be compared with independent *t*-test and Mann–Whitney test as appropriate at two and five years follow-up. Subgroup analyses for the two fracture groups B2 and C2 are planned to gain further information of effectiveness of treatment. Multiple imputation will be used to handle missing values. The QALY analysis from 15D outcome will be performed according to the specific 15D syntax for SPSS and completed with a one-way sensitivity analysis for each variable in the analysis.

The intention-to-treat principle will be adopted: Patients will be analysed according to their initial treatment group in case of cross over to the other group.

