### Health related quality of life 15D

We use Harri Sintonen’s “15D”, a generic, self-administered instrument to assess Health Related Quality of Life (HRQoL) [63]. It encompasses 15 dimensions of health. The dimensions are moving, seeing, hearing, breathing, sleeping, eating, speech, eliminating, usual activities, mental function, feeling of discomfort, depression, distress, vitality and sexual activity. The questionnaire is modified, as the last dimension sexual activity is omitted, as some elderly patients may feel uncomfortable with this question. This score is validated and modifications in the statistical syntax for calculation of the score has been made to avoid confounding the outcome (http://www.15D-instrument.net). The scores along the 15 dimensions are translated into a zero-to-one quality of life index by means of an algorithm where zero represents death and 1.0 represents perfect health.

On admission to hospital, the patients will be asked to report their HRQoL as it was immediately before the fracture, and it will be repeated at 6 months, one, two and five years follow-up.

Quality adjusted life-years (QALYs) will be calculated for each patient by multiplying the time spent in a health-condition since the last follow-up by the HRQoL of this condition using the 15D scores (Additional file 1).

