### Method of randomization

Randomization is performed by the NTNU web-CRF solution with separate blocks and stratification to age and gender for each collaborating hospital.

(https://webcrf.medisin.ntnu.no/client/index.php). Randomization of a new patient in one of the participating hospitals will generate a coded message to the project group with information of treatment and inclusion number for this hospital.

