## Discussion

This protocol has been designed according to recommendations given by the Consort group [4]. The design of a randomized controlled study with a high level of evidence including more than 100 patients, with semi-blinded independent physical therapists collecting patient data gain important knowledge about proximal humeral fractures. A standardized surgical approach for both groups without compromising the deltoid muscle, reduces group differences, and a standarized educational program for all physiotherapists prior to examination of patients at follow-up contribute to a better methodological design and strengthen this study.

This study protocol has been adjusted according to our experience from former studies, both regarding outcomes, method of randomization and exclusion criterias [16, 17]. Also, to gain knowledge of the external validity of this study, all patients aged 65 to 85 years admitted to two of the recruiting hospitals will be grouped according to the exclusion criteria and AO classification, hopefully increasing our knowledge of the generalizability of our results. This generalizability and the question if the results of this trial will cause impact in the future treatment of displaced B2 and C2 proximal humeral fractures is a basic issue when a new trial is designed. Although it is more than 40 years since Charles Neer wrote his two important papers on classification and treatment of proximal humeral fractures, these papers are still frequently referred and the treatment is still under debate [1, 2]. The sparse number of studies at the highest level of evidence may be one of the reasons.

The trial may have potential weaknesses: Blinding of a trained physiotherapist examining a patient with a prosthetic replacement is difficult due to the mechanics of the implant. Another potential problem is that the primary outcome (Constant score) has a low reproducibility between different observers in a multicenter trial [67, 68]. However, the pre-trial training for all participating physiotherapists will reduce this bias.

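### Randomisation is stratified by hospital, age and gender, but the stated comparison of the arms adjusts for none of them, which may cost a little precision

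*Protocol article*

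**What the plan says.** **Design.** Under Method of randomization, patients are allocated "with separate blocks and stratification to age and gender for each collaborating hospital".

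**Analysis.** Under Statistics: "Mean differences between the groups will be compared with independent" t-test and Mann–Whitney test as appropriate, at two and five years. No stratification factor is named. Means with confidence intervals are reported per hospital and overall, and B2 and C2 fractures are analysed as subgroups.

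**Are the factors prognostic?** The section on the primary outcome introduces the injured-minus-uninjured difference (CSD) to lessen the effect of age. It also lists a Constant score adjusted for age and gender as a secondary outcome. The Discussion concedes that "the primary outcome (Constant score) has a low reproducibility between different observers in a multicenter trial" and then says that training before the trial will reduce this.

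**Sizing.** Power of the trial and sample size states "we used the primary outcome Constant Shoulder Score with a range from zero to 100 points", and adds "SD equals18 according to clinical experience" and "The minimal clinically important difference has been decided to equal 10 points". With α 0.05 and power 0.80 this gives 51 per group, raised to 60 for expected loss.

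**15D.** The 15D section says "On admission to hospital, the patients will be asked to report their HRQoL as it was immediately before the fracture", so a baseline value exists for that outcome.

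**The concern.** Stratified blocks make the arms more alike on the stratification factors than simple randomisation would. When those factors predict the outcome, the estimated difference between arms varies less from trial to trial. An independent t-test does not know this. It leaves the variation due to hospital, age and gender in the error term and so computes too large a standard error. The test then rejects less often than 5% under the null, its intervals cover more than 95%, and power that the design has already paid for goes unused.

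The article gives grounds to expect some prognostic effect. It treats age and gender as influences on the score and observer differences as a multicentre problem. Physiotherapists from all centres were trained for the trial, so observer differences plausibly follow hospital, although that link is an inference. The trial is sized at 80% power with no margin beyond expected loss, so a small gain at no cost in data is worth having.

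**Working it through.** **1. Inputs.** From the article: difference 10 points, SD 18, α 0.05, power 0.80, 51 per group. Sidedness is not stated. Assumed, because the article does not give them: R² (the share of Constant score variance explained by hospital, age and gender) of 0, 0.10 and 0.20; two age strata; blocks of 4; seven hospitals. The abstract says seven hospitals and Method of inclusion says six.

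**2. The article's own figure.** Two-sided normal approximation:

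n = 2 × (1.960 + 0.842)² × 18² / 10² = 50.9, so 51 per group.

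This matches. A one-sided test would give 41. The exact t-test gives 51.8. Allowing 15% loss, 51 / 0.85 = 60. The stated sample size reproduces from an unadjusted comparison.

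**3. Idealised gain from adjustment.** Residual SD = 18 × √(1 − R²); CI half-width = 1.96 × residual SD × √(2/51).

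| R² | Residual SD | Half-width (points) | Power, 51 per group |
|---|---|---|---|
| 0 | 18.00 | 6.99 | 0.801 |
| 0.10 | 17.08 | 6.63 | 0.841 |
| 0.20 | 16.10 | 6.25 | 0.880 |

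These figures ignore the parameters spent on covariates and any imbalance within strata.

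**4. Simulation with incomplete blocks.** 102 patients, 7 × 2 × 2 = 28 strata, 3,000 runs per setting, explained variance split equally over the three factors. The adjusted model is linear, with treatment, hospital, age and gender as main effects.

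| R² | t-test type I error | Power: t-test | Power: Mann–Whitney | Power: adjusted | 95% CI full width: unadjusted / adjusted |
|---|---|---|---|---|---|
| 0 | 0.053 | 0.79 | 0.78 | 0.78 | 14.1 / 14.3 |
| 0.10 | 0.041 | 0.80 | 0.78 | 0.82 | 14.1 / 13.6 |
| 0.20 | 0.038 | 0.81 | 0.79 | 0.87 | 14.1 / 12.7 |

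The Monte Carlo standard error of a type I error near 0.05 is √(0.05 × 0.95 / 3000) = 0.004. Repeat simulations under the same assumptions gave 0.040 to 0.043 at R² = 0.10 and 0.034 to 0.037 at 0.20. One repeat gave power of 0.80 against 0.86 at R² = 0.20. Coverage of the unadjusted interval under the null was 0.959 and 0.962 at R² = 0.10 and 0.20. The adjusted model kept type I error between 0.049 and 0.055 and coverage near 0.95.

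**5. Why the simulated effect is milder than the ideal one.** With perfect balance in every stratum, the t-test's type I error would be 2 × P(Z > 1.984 / √(1 − R²)), which is 0.037 at R² = 0.10 and 0.027 at 0.20. But 102 patients over 28 strata average 102 / 28 = 3.6 per stratum, below one assumed block of 4. Many blocks stay incomplete and balance is only partial.

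**The case against.** **The effect is small, conservative and rests on an assumption.** R² appears nowhere in the article. At R² = 0 adjustment loses about one power point, and at 0.10 it gains about two. The power figures also use 51 per arm, the number left after all expected loss. With 60 per arm and no loss, the unadjusted t-test already has power of 0.855. All of this stands and limits the weight of the point.

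**The outcome definition already does part of the work.** CSD subtracts the uninjured shoulder, and the same physiotherapist scores both sides. If CSD is analysed, part of the age effect and any constant assessor offset would drop out. The sample size is built on the injured-shoulder score, so this reduces the point without removing it. The age- and gender-adjusted score is a secondary outcome, not an adjusted comparison of the arms.

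**Covariates can be left to a statistical analysis plan.** A plan not shown here may add the adjustment. The article does not leave the test open, however: it names one that does not match its randomisation.

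**Stronger readings.** A reader might infer that type I error falls to 0.027 at R² = 0.20. That needs perfect balance within strata, which such sparse strata cannot be expected to deliver. A reader might also fault the unspecified choice between t-test and Mann–Whitney, the pooling of rank tests after imputation, or the lack of a fracture-group covariate. None of these follows from the stratification mismatch. The test sentence covers all outcomes, so the choice can be read as one made by outcome type. Pooling rules are commonly left to an analysis plan. Fracture group is not a stratification factor, and its subgroup analysis is already planned.

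**Conclusion.** The point holds as a modest loss of efficiency. The article stratifies by age and gender within hospital and then states a comparison that uses none of these factors. Neither the per-hospital means, the B2/C2 subgroups nor the derived Constant scores supply an adjusted comparison.

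For assumed R² of 0 to 0.20, 51 per arm and incomplete blocks, the t-test's type I error runs from about 0.05 to about 0.037. Adjustment changes power by about −1, +2 and +6 points at R² = 0, 0.10 and 0.20. The 95% CI narrows by about 4% at 0.10 (14.1 to 13.6) and 10% at 0.20 (14.1 to 12.7). The gain from age would be smaller if CSD is analysed. The figures also rest on the assumed strata, block size and number of hospitals.

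A reader might take the mismatch to mean that the trial risks a false positive or is wrongly sized. The documents support neither: the error is in the conservative direction, and 51 per group reproduces exactly.

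**What to change.** Make the primary comparison a linear model for the Constant score with treatment, hospital, age and gender as main effects, and report the adjusted mean difference with its 95% CI. Enter hospital as a fixed or random effect. Do not fit the full set of strata, because up to 28 cells for 120 patients are too sparse. Keep the unadjusted t-test or Mann–Whitney test as a sensitivity analysis. For 15D, the pre-fracture value already collected can be added as a covariate. If an analysis plan already specifies such a model, bring the protocol wording into line with it.

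The cost is wording only. The stratification factors are known at randomisation, so no new data are needed. With seven hospitals the model has about ten parameters (intercept, treatment, six for hospital, one each for age and gender: 1 + 1 + 6 + 1 + 1 = 10). If the factors turn out not to be prognostic, this loses roughly one power point.

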Although numerous studies exist dealing with proximal humeral fractures, most of them represent level IV evidence [15]. Thus, interpretation must be made with caution and evidence is at present too limited to support secure recommendations for treatment, even including if surgical treatment is superior to conservative for severely displaced fractures. The number of level I and II trials in this field are few. In our department we recently completed a single center randomized controlled study of displaced proximal humeral fractures; an angular stable plate was compared to conservative treatment. After two years follow-up we could not detect any significant differences between surgery and conservative treatment with regard to physical functioning and health-related quality of life [16, 17]. Nevertheless, there is evidence that the rate of surgical treatment has increased significantly in the period from 1999 to 2005 [18].

The proximal humeral fracture groups comprise two-, three,- or four part fractures: non-displaced, displaced or displaced with dislocation (AO-OTA type A,B and C) [19]. Many proximal humeral fractures are minimally displaced, and should not be considered for surgical treatment. About one fifth are displaced 3- and 4 part fractures (AO-OTA group B2 and C2) [7]. In these fractures many surgeons perform operative treatment, even if this has not been proven superior to a conservative approach except from in certain displaced fracture dislocations, where surgery may be favorable [3]. However, most orthopaedic surgeons agree that classification and differentiation of the main groups of proximal humeral fractures are important for treatment decision making, as prognosis and the technical challenges depend on the fracture displacement and comminution [20, 21].

If surgery is decided, the most frequent treatment modalities are open reduction and internal fixation with an angular stable plate, a locked intramedullary nail, or in some patients minimally open surgery with screws, threaded pins and sometimes cerclage wires. Shoulder hemi-artroplasty has also been widely used [22–32]. Although numerous surgical options exist for the displaced fractures, none has yet proven to be superior [3, 33–35]. Also, several complications and impaired shoulder function are reported after different types of surgical treatment [36–43].

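### B2 and C2 subgroup analyses are planned without saying how the two effects will be compared; if each is tested alone, a uniform 10-point effect is significant in only one about half the time

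*Protocol article*

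**What the plan says.** The Statistics section of the protocol article compares the two treatment groups by t-test or Mann–Whitney test at two and five years, and plans means with 95% confidence intervals, bootstrapped where groups are small. It then adds: "Subgroup analyses for the two fracture groups B2 and C2 are planned to gain further information of effectiveness of treatment". No test, model or rule of interpretation is attached to that sentence. No regression model or covariate appears in the section.

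The sample size, under Power of the trial and sample size, concerns the overall comparison only: "The minimal clinically important difference has been decided to equal 10 points" and "Given a power of 0.80 (β) the number required in each group is 51 patients".

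Under Method of randomization the listed factors are "stratification to age and gender for each collaborating hospital"; fracture group is not among them. Radiographic evaluation says fractures will be classified to AO/OTA group and subgroup, and Method of inclusion has the radiographs confirmed centrally before randomization. Fracture group is therefore recorded as a baseline variable.

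**The concern.** The subgroup analyses are meant to inform effectiveness, yet the only comparison tests named cannot answer the question that two subgroups raise, which is whether the treatment effect differs between them. Each test compares the arms within one set of patients. If it is run once in B2 and once in C2, the tempting summary is that the prosthesis works in one fracture type and not in the other. A significant result beside a non-significant one is not evidence that the effects differ, and with about half the trial in each subgroup that pattern is common by chance.

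What is at stake is the reading of a secondary result: a benefit that is the same in both fracture types could be reported as confined to one of them.

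**Working it through.** **Inputs from Power of the trial and sample size.** Constant score, 0 to 100 ("To calculate the sample size we used the primary outcome Constant Shoulder Score with a range from zero to 100 points"); "SD equals18 according to clinical experience"; difference 10 points; "Level of significance (α) equals 0.05", sidedness not stated; power 0.80; 51 per arm required, 60 recruited.

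**Assumption.** The B2:C2 split is not given. I take 50:50 as the base case and show splits to 20:80.

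**1. The plan's own figure.** n = 2 × (1.96 + 0.8416)² × 18² / 10² = 2 × 7.849 × 3.24 = 50.9, so 51 per arm. This matches, and shows that the test is two-sided (one-sided gives 41). 51/60 = 0.85, an implied allowance for loss of 15%.

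**2. Power within one subgroup, even split.**
- 51 per arm gives 25.5 per arm per subgroup. SE = 18 × √(2/25.5) = 5.04; 10/5.04 = 1.984; power = Φ(1.984 − 1.96) = 0.51 (noncentral t: 0.49).
- 60 per arm gives 30. SE = 18 × √(2/30) = 4.65; 10/4.65 = 2.152; power = Φ(0.192) = 0.58 (noncentral t: 0.56).

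**3. Chance that exactly one subgroup is significant, true effect 10 points in both.** The subgroups are independent, so P = p₁(1 − p₂) + p₂(1 − p₁). At 51 per arm with p = 0.494: 2 × 0.494 × 0.506 = 0.50.

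| B2:C2 split | 51 per arm | 60 per arm |
|---|---|---|
| 50:50 | 0.50 | 0.49 |
| 40:60 | 0.51 | 0.50–0.51 |
| 30:70 | 0.55 | 0.55–0.56 |
| 20:80 | 0.61 | 0.63 |

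Ranges span the normal and noncentral t calculations. Among trials with a significant overall result, a simulation of 10⁶ runs gives 0.57 (51 per arm) and 0.53 (60 per arm) at an even split.

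**4. Other uniform effects, even split, noncentral t.**

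| True effect in both (points) | 51 per arm | 60 per arm |
|---|---|---|
| 0 | 0.10 | 0.10 |
| 5 | 0.27 | 0.30 |
| 8 | 0.45 | 0.48 |
| 10 | 0.50 | 0.49 |
| 12 | 0.46 | 0.40 |
| 15 | 0.28 | 0.20 |

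**5. Interaction test.** When the effect is uniform it declares a difference in 5% of trials (simulated 0.050). Its precision at an even split:
- 51 per arm: SE of the difference in effects = 18 × √(4/25.5) = 7.13; 95% CI ± 1.96 × 7.13 = ± 14.0 points; power for a 10-point difference in effects = Φ(10/7.13 − 1.96) = 0.29; 80% power needs 2.80 × 7.13 = 20 points.
- 60 per arm: SE = 18 × √(4/30) = 6.57; ± 12.9 points; power 0.33; 80% power needs 18 points.

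All figures are for one time point.

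**The case against.** The strongest reply is that the article is silent on the subgroup method rather than wrong about it. It is a condensed account, and a full protocol or analysis plan may specify an interaction. That stands. A reader might infer that the plan has decided on separate tests and rules an interaction out, but the text does neither. The tests are named for the treatment comparison, and the subgroup sentence names none. The figures above are therefore conditional on the only named tests being run within each fracture group.

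Two other inferences are tempting and not supported.
- That the Discussion promises treatment recommendations by fracture type. It mentions B2 and C2 together, as the trial population, in a remark on generalizability.
- That leaving fracture group out of the stratification leaves the within-subgroup comparisons uncontrolled. Randomization still makes each of them unbiased, and within B2 alone or C2 alone fracture group is constant, so stratifying on it or adjusting for it would correct nothing there. The Background sentence that "prognosis and the technical challenges depend on the fracture displacement and comminution" does not name B2 against C2. It gives a reason to expect some gain in precision from a fracture-group term in the overall model, and no more.

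It is also fair to say that the article plans confidence intervals and never adopts a significant/not-significant reading, and that the subgroup analysis is worded as supplementary. Both limit the weight of the point. Neither says how the two effects are to be compared.

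**Conclusion.** The point holds as a cheap improvement to a supplementary analysis, and it does not touch the validity of the overall comparison. The article commits to B2 and C2 analyses of effectiveness and names no method able to compare the two effects.

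If the named tests are run within each fracture group, a pattern that looks like a differential effect arises in about half of trials in which the effect is in fact uniform, against 5% for an interaction test. The half rests on a true effect near 10 points, SD 18, 51 to 60 per arm and an even split. It rises with an uneven split and falls to between 0.20 and 0.30 at uniform effects of 5 or 15 points, so it should not be quoted for a uniform effect of any size.

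**What to change.** State that the B2 and C2 effects will be compared through a treatment-by-fracture-group interaction in a linear model for the Constant score. Report the effect in B2, the effect in C2 and their difference, each with a 95% CI. Label the result exploratory, and say that no conclusion will be drawn from one subgroup being significant and the other not. Also include fracture group as a main effect in a linear model for the overall comparison, since it is already collected before treatment.

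The cost is in the analysis only: no patients, visits or data are added. It is slightly more than a change of wording, because the article describes no linear model. One must be added beside the t-test or in its place, and which of the two is primary should be fixed before outcome data are seen. The interaction will usually be inconclusive (power 0.29–0.33 for a 10-point difference in effects, interval about ± 13 to ± 14 points at an even split). The plan should say so in advance, so that a non-significant interaction is not read as proof that the effects are equal.
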